### Identification and description of factors

3.3

In the initial phase of the study, risk-predicting parameters will be defined using data from the CAMUS Collaboration cystectomy database, which will include pre- and intraoperative variables sourced from 178 centres worldwide. Additional parameters from a prospective open cystectomy database maintained by the Urology Department at the University of Bern will further enhance data collection. The difficulty estimation score will be developed and validated using these data, supplemented by prospectively collected parameters detailed in round 1 of the study.

The RC cohort will be selected as the primary focus due to its high complication rate and clinical relevance. In subsequent phases, the scoring system’s performance will be assessed in various patient cohorts who have undergone RP, PN, radical nephrectomy (RN), radical nephroureterectomy (RNU), and retroperitoneal lymph node dissection (RPLND).

The first Delphi round will involve expert consensus to identify parameters influencing peri- and postoperative morbidity, mortality, and surgical difficulty. For example, parameters relevant to RP will be outlined in Supplementary Tables 1 and 2. Experts will be guided by the results derived from nomograms. Organ-specific factors, as part of the organ-specific scoring system, will also be examined for procedures such as RC, RP, PN, RN, RNU, and RPLND, with further details provided in Supplementary Table 3.

To assess the impact of these parameters on both difficulty and risk, a comprehensive description of the associated conditions and characteristics will be required. These parameters will be categorised according to a five-level scale of difficulty: easiest, intermediate easy, standard, intermediate difficult, and most difficult. For instance, preoperative BMI ranges will be classified as follows: BMI 18–22 kg/m^2^ will correspond to the easiest grade, while BMI >40 kg/m^2^ will be categorised as most difficult. Similarly, for organ-specific factors such as prostate size in RP, a prostate volume of 20–30 cc on magnetic resonance imaging will represent the easiest level of difficulty, whereas a volume exceeding 200 cc will be classified as most difficult.

Notably, multiple conditions may be associated with the same level of difficulty. For example, multiple prior open procedures or laparoscopic surgeries involving mesh insertion may be considered of intermediate difficulty.

In the second Delphi round, the complexity range (difficulty/risk) associated with each identified factor will be refined further. Experts will evaluate the significance of each factor concerning morbidity, mortality, and surgical difficulty using a numerical scale. Separate ratings will be assigned for risk estimation and surgical difficulty, ranging from 0 to 10. A rating of 0 will indicate no impact on surgical difficulty or risk, whereas a rating of 10 will signify a strong association with significant surgical difficulty and a near-certain major complication. For example, the difficulty of tissue plane dissection might be rated as follows: completely adherent planes (9), normal planes (5), and easily identifiable and dissectable planes (0).

Through the Delphi process, consensus will be reached regarding key parameters, their specific conditions and manifestations, and their quantified impact (0–10) on risk and surgical difficulty. These consensus parameters will be integrated into the risk and difficulty indices, which will be calculated automatically.

In clinical practice, surgeons will assess these parameters both preoperatively and postoperatively. Rather than assigning numerical values, surgeons will evaluate these according to a structured risk and difficulty scale (0–5), as outlined above. This approach will streamline decision-making and facilitate practical application of the indices.

### Clinical scenario for rating general and targeted organ-specific parameters in RP

3.4

Preoperatively known general and targeted organ-specific factors will be entered into a computer system or calculator. Their impact on risk and surgical difficulty will be assessed and recorded separately.

For instance, a prostate size of 40 cc will correlate with a surgical difficulty rating of 2 (intermediate easy), while prior laparoscopic procedures involving tissue resection (eg, bowel anastomosis) or mesh insertion will be classified as standard difficulty (grade 3).

In terms of peri- and postoperative risk estimation, well-controlled diabetes will be assigned a grade 1 condition.

As outlined previously, preoperative risk and difficulty estimation for RP will be conducted based on the general and organ-specific factors identified preoperatively. Immediately postoperatively, the surgeon will update risk and difficulty estimates based on intraoperative conditions. For example, if tissue planes are classified as partially adherent, partially identifiable, and dissectible, a standard difficulty rating (grade 3) will be recorded. If significant bleeding occurs without clotting but with intact vision, a grade 4 (intermediate difficulty) condition will be noted. For intraoperative parameters influencing peri- and postoperative risks, blood loss ranging from 100 to 500 ml will be considered a grade 2 condition.

To further refine the morbidity and mortality risk estimation following RP, postoperative conditions occurring prior to discharge or within 24 h will be entered into the system. A decrease in glomerular filtration rate by 60% will be classified as a grade 4 condition.

### Weighing of factors

3.5

Once consensus has been reached on the parameters for developing the risk and difficulty stratification tool, both surgeons and anaesthetists will assign weights to each parameter. These weights will be represented as ws + wa = (weight of the surgeon × weight of the anaesthetist), where “ws” denotes the weight assigned by the surgeon and “wa” the weight assigned by the anaesthetist. The weighting will depend on whether the parameter is assessed by both specialists or exclusively by one discipline.

Parameters will be assigned separate weights for surgical difficulty and risk of complications. The weighting system will be structured so that parameters with a low likelihood of complications, those associated with less severe complications (eg, conditions manageable through perioperative interventions), or those resulting in minimal intraoperative difficulty are assigned lower values. Conversely, parameters with a higher likelihood of complications, greater severity, or increased intraoperative difficulty will be allocated higher values.

### Development of the risk and difficulty stratification index

3.6

Following the consensus phase, the next step is to develop the formula for the risk prediction index. In this phase, the weights assigned by both surgeons and anaesthetists (ie, the median reference value) will be incorporated into a formula, which will then be normalised to a value ranging from 0 to 100. Similar to the Comprehensive Complication Index (CCI) formula [23,24], variables may be included to ensure that the model assigns higher values for multiple and severe complications while yielding lower values for single and minor peri- and postoperative complications. This approach will enhance the precision of differentiating between the severity and impact of pre- and postoperative risk factors. Organ-specific scoring systems will be developed following the same methodology.

Based on the outcomes of the Delphi process, we will determine whether a single formula or index is sufficient to address all three objectives outlined or whether multiple indices are required. Specifically, one index may be necessary to assess preoperative factors alone (eg, to enhance decision-making, optimise the allocation of critical care resources, or designate surgeries as teaching cases), while another index may be needed to incorporate both pre- and intraoperative factors for broader objectives. If surgical difficulty requires an independent calculation, a third distinct index may be warranted.

As highlighted previously, a surgeon’s learning curve—defined by a cumulative case volume—is a critical factor. This curve will be stratified into experience-based stages: 0–20 cases, 21–50 cases, 51–100 cases, 101–250 cases, 251–500 cases, and >500 cases. Proficiency typically plateaus after approximately 500 cases.

The assertion that surgical proficiency plateaus after around 500 cases is supported by studies analysing learning curves in complex surgical procedures. Research using a cumulative sum (CUSUM) analysis and other models has demonstrated that significant improvements in performance metrics—such as operative time, complication rates, and technical outcomes—tend to stabilise after approximately 500 cases, particularly in highly complex surgeries [25,26].

This stratification serves two purposes: (1) it allows the estimation of how increasing surgical experience reduces case difficulty and risk, and (2) it helps determine whether a procedure is suitable for a teaching setting.

It is essential to differentiate between the absolute and relative risks within this framework. Certain patient-specific factors, such as prior radiation therapy, inherently elevate the absolute risk and case difficulty. However, a highly experienced surgeon (eg, one with >500 completed cases) can mitigate these challenges in relative terms. Consequently, the calculated risk and difficulty index for a given case may be adjusted downward when performed by an experienced surgeon, incorporating their proficiency into the assessment model.

### Data collection

3.7

The CAMUS Collaboration has established four independent outcome databases for patients undergoing open or minimally invasive RC, RP, PN, RN, RNU, and RPLND, This collaborative study has collected various pre-, intra-, and postoperative outcome variables, along with complication data (including complication type, intervention, and grading), to evaluate their potential as predictors for intra- and perioperative risk estimation. Additionally, a comprehensive single-centre cystectomy database from the University Hospital Bern (*n* = 1550) is included. In more detail, the CAMUS database includes a diverse patient population from various centres, reflecting a wide range of clinical scenarios and surgical outcomes. To minimise the potential selection bias, the exclusion criteria were restricted to patients with ≤10% missing data and by age factor, allowing the inclusion of all patients aged 18 yr and older. This approach ensures a representative cohort and enhances the generalisability of our results.

The required sample size was estimated using a power-based method for logistic regression models, considering the number of predictor variables ranging from 10 to 30 (refer to section 6.1 for more information). The calculations were performed using the pwr package [1] in the statistics software R, version 4.4.2 [2], utilising effect sizes based on assumed odds ratios of 1.2 (weak effect), 1.5 (moderate effect), and 2.0 (strong effect). The required sample size is reached when a statistical power of at least 80% is achieved at an alpha level of 0.05. To enable internal validation (see section 6.3), the final sample size was increased by 50%, ensuring sufficient data for both model training and validation. Consequently, the most extreme case—30 predictors with a weak effect size (odds ratio = 1.2)—required a sample size of 1180, which is well below the available sample size.

Patients eligible for inclusion are aged 18 yr or older.

Data collection has been conducted by trained and audited registrars, consultants, and study nurses at each participating hospital, ensuring standardised data definitions across all institutions. Missing data have been managed using imputation, specifically employing the Buck’s method. Patients with missing values for critical variables—such as the date of postoperative complication-intervention events, Clavien-Dindo complication (CDC) grade, or death within 90 d—have been excluded from the analysis.

For inclusion in the initial patient cohort (cohort 1), all patients who underwent open or minimally invasive RC and urinary diversion between 2000 and 2021 were selected. Cohort 2 includes all patients who underwent open or minimally invasive RP between 2000 and 2020. Cohort 3 comprises all patients who underwent PN, RN, RNU, and RPLND. All variables from the CAMUS database have been included in the analysis.

Certain variables were adjusted for analytical purposes, such as categorising renal function into grades 1–5 and grouping intervention events (eg, intensive care treatment) into broader categories with subgroups (eg, cardiac and pulmonary intensive care). These adjustments were made to establish preoperative comorbidity categories and transform non-normally distributed variables. The primary study outcomes are the CDC/CAMUS grade or death within 90 d and the Comprehensive Complication Index (CCI).

Preoperative (expected/known) risk and difficulty factors used to calculate patient-specific risks and surgical difficulty were selected a priori based on their predictive value, routine availability to the surgeon before the operation, and clinical face validity. Similarly, intraoperative (unexpected/unknown) risk and difficulty factors were selected based on their predictive value, the surgeon’s expertise, and clinical validity. Immediate postoperative factors that refine risk estimation follow the same methodology.

All preoperative, intraoperative, and immediate postoperative factors will be evaluated using the Delphi method, as described previously.

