**Table 2 t0010:** Proposed CAMUS intra- and postoperative risk and difficulty estimation indices (IPRADES)

CAMUS IPRADES indices								
Non–organ-specific factors impacting surgical difficulty and risk for complication								
No.	Expected/known (preoperative) parameters				Unexpected/unknown (intraoperative) parameters			
	Parameter	Surgeon		Anaesthetist	Parameter	Surgeon		Anaesthetist
		Surgical difficulty (0 = no, 1 = yes)	Risk for complication (0 = no, 1 = yes)	Risk of complication (0 = no, 1 = yes)		Surgical difficulty (0 = no, 1 = yes)	Risk for complication (0 = no, 1 = yes)	Risk of complication (0 = no, 1 = yes)
1	Diabetes				Intraoperative fluids administered (ml)			
2	ASA classification				Estimated blood loss (ml)			
3	Timing of surgery (AM, PM)				Duration of operation (min)			
4	BMI (kg/m^2^)				ECG abnormalities			
5	Anticoagulant agents				Ventilation difficulties			
6	Elective vs emergency				General overall tissue quality			
7	Previous therapy: non–organ-specific (eg, radiation)				Ooziness/tissue vascularity			
8	Charlson Comorbidity Index				Scarred tissue			
9	Prior abdominal surgical history + type of surgery (eg, bowel resection vs cholecystectomy)				Adherent tissue			
10	Nutrition status (eg, albumin, weight loss, cachexia)				Identifiable planes			
11	Age				Vision			
12	Gender				Vessel injury			
13	Steroid use for chronic condition				Intraoperative blood transfusion			
14	Smoking status				–			
15	Further parameters to be proposed by Delphi experts				Further parameters to be proposed by Delphi experts			
Unexpected/unknown (immediate postoperative) parameters								

Parameter		Surgeon				Anaesthetist		
		Risk for complication (0 = no, 1 = yes)				Risk of complication (0 = no, 1 = yes)		

Acute kidney injury (ie, eGFR decrease by 10 ml/min)								
Significant demand for analgesia (ie, opioids >50 μg)								
Targeted organ-specific factors impacting surgical difficulty and risk for complication (organ-specific scoring system) shown in an exemplary way for laparoscopic/robotic radical prostatectomy								
	Expected/known (preoperative) parameters				Unexpected/unknown (intraoperative) parameters			
	Parameter	Surgeon			Parameter	Surgeon		
		Surgical difficulty (0 = no, 1 = yes)	Risk for complication 0 = no, 1 = yes)			Surgical difficulty (0 = no, 1 = yes)	Risk for complication (0 = no, 1 = yes)	
1	Prostatic size (cc) on MRI (eg, very small or very large)				Narrow bony pelvis			

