### Internal validation

4.3

Internal validation of the prediction models will be conducted by randomly splitting the analytic dataset into two subsets: a developmental dataset (two-thirds of the total data) and a validation dataset (one-third of the total data). The C-indices, HL analyses, and Brier scores from the logistic regression analyses will be compared between the developmental model applied to the developmental dataset and the same model applied to the validation dataset.

The use of stepwise, forward-selection logistic regression has faced criticism, particularly in small samples, regarding variable selection and the accuracy of the coefficients and standard errors. However, such criticisms are less relevant when applied to the large sample sizes present in this study. To further test the robustness of the model, bootstrap resampling will be employed for the postoperative mortality model. Full-variable logistic regression models will be performed on each bootstrap sample. The variables will then be ranked by the magnitude of the Wald χ^2^ statistic, and the average rankings from the bootstrap samples will be compared with the order of entry of variables during the forward selection stepwise regression analysis. As such, all steps described above aim to minimise overfitting and improve predictive accuracy.

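### The sample size of 1180 for 30 predictors at an odds ratio of 1.2 uses no stated event fraction, matches a linear-regression test, and is too small to detect a single such predictor in logistic regression

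*Protocol article*

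**What the plan says.** Section 3.7 (Data collection) says the sample size was "estimated using a power-based method for logistic regression models", "considering the number of predictor variables ranging from 10 to 30". It names the software: "The calculations were performed using the pwr package". The assumed odds ratios are 1.2, 1.5 and 2.0, and the criterion is: "The required sample size is reached when a statistical power of at least 80% is achieved at an alpha level of 0.05". The result was raised by 50% to allow internal validation. The hardest case, 30 predictors at an odds ratio of 1.2, "required a sample size of 1180, which is well below the available sample size".

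No event fraction, predictor scale or correlation among predictors is given. The text does not say whether power refers to one predictor or to the model as a whole. The only patient count in the article is 1550, for the Bern cystectomy database.

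Section 4.1 selects variables by p value: a univariate screen at 0.20, then stepwise entry at 0.10 and inclusion at 0.05, with AIC for the final model. The β coefficients then become score weights. Section 4.3 sets aside the usual objections to stepwise selection because "such criticisms are less relevant when applied to the large sample sizes present in this study". Table 2 lists the proposed parameters, and each of its pre- and intraoperative lists ends with "Further parameters to be proposed by Delphi experts".

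**The concern.** In logistic regression the information about a coefficient is proportional to p(1−p), where p is the event fraction. A sample size stated without p therefore cannot be checked against the method named, and it may come from a different model. If 1180 is too small for the selection the plan performs, real predictors of modest strength will often be missed. Those retained will tend to have exaggerated coefficients, which pass directly into the score. The reassurance that the data are ample would also lose its stated basis. Calling 30 predictors the most extreme case matters for the same reason, because the plan itself proposes more candidates than that.

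**Working it through.** **Inputs from the documents.** Odds ratio 1.2, so b = ln 1.2 = 0.1823 and b² = 0.03324; 30 predictors; α = 0.05 (two-sided assumed); power 80%; inflation × 1.5; stated total 1180, so 1180 / 1.5 = 787 for development, which agrees with the two-thirds split in section 4.3.

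**Assumed, because not given.** The odds ratio is per standard deviation of a predictor uncorrelated with the others. Event fractions are shown as a range.

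**1. Reproducing 1180.** Take the overall F test of a linear regression with u = 30, noncentrality f²(u + v + 1) and N = u + v + 1. With f² = b²/(1 + b²) = 0.0322, 80% power gives v = 754.1, so N = 786 and 786 × 1.5 = 1179. With f² = b² the result is 761 × 1.5, about 1142, which is further off. The code is not shown, so this is a reconstruction. It treats a log odds ratio as a linear slope and contains no event fraction.

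**2. One predictor in logistic regression.** n = (1.960 + 0.842)² / [p(1−p)b²]; power at n is Φ(b√(n p(1−p)) − 1.960). Totals are 1.5 times the unrounded n, rounded up.

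| Event fraction | Development n | Total | Power at 787 |
|---|---|---|---|
| 50% | 945 | 1417 | 72% |
| 30% | 1125 | 1687 | 65% |
| 20% | 1476 | 2214 | 53% |
| 10% | 2624 | 3936 | 33% |

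At 50%, for example: 7.849 / (0.25 × 0.03324) = 944.5. This is the minimum over all event fractions, and it exceeds 787. If the odds ratio refers to a balanced binary predictor instead, the total is 5685 with a 50% risk in the reference group.

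**3. Whole-model tests in logistic regression.** The 30-df noncentrality for 80% power is 24.55.
- If the total signal is that of one odds-ratio-1.2 predictor, as in step 1, n = 24.55 / [p(1−p)b²]: a total of 4431 at 50% events and 6923 at 20%.
- If all 30 independent predictors each have odds ratio 1.2, n = 24.55 / [p(1−p) × 30b²]: about 98 at 50% events and 154 at 20%, before inflation.

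Neither gives 1180.

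**4. Number of candidates.** Table 2 lists 14 preoperative, 13 intraoperative and 2 immediate postoperative general parameters, plus 12 and 13 for the prostatectomy example: 14 + 13 + 2 + 12 + 13 = 54 rows, or 53 distinct because BMI appears twice. The method of step 1 with u = 53 gives 998 × 1.5 = 1497.

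**5. The available sample.** Two-thirds of 1550 is 1033. Setting n = 1033 in step 2 requires p(1−p) ≥ 7.849 / (0.03324 × 1033) = 0.229, that is, p between about 35% and 65%.

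**The case against.** The strongest reply is that section 3.7 does not say what the power refers to. If all 30 predictors are independent and each has odds ratio 1.2, a global logistic test needs about 98 to 154 patients (50% to 20% events). Even at 5% events it needs about 518, or 777 after inflation, so 1180 would be generous. This stands as arithmetic. But that reading does not produce 1180, and showing that some signal exists somewhere among 30 predictors does not justify choosing predictors one at a time.

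Second, 1180 is a minimum, not the sample to be analysed. Bern alone would give 1033 development patients, with single-predictor power of 82% to 83% at 40% to 50% events and 65% at 20%, and the CAMUS data come on top. If all 1180 were used for development, 80% power would be reached at event rates of about 28% or more. These points stand too, but the plan reserves a third for validation and gives no CAMUS count.

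Third, section 3.7 refers to a section 6.1 that is not in the article, so an event rate may have been considered there. This cannot be excluded, but the single-predictor minimum exceeds 787 at every event rate.

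A reader might also infer more than the documents support:
- **That 53 candidates make the 30-predictor figure wrong.** They do not; they show only that 30 is not the ceiling. The count belongs to the prostatectomy example, and the parameters are proposals still to be voted on. The general list has 29 rows, within the stated range.
- **That the models will be badly overfitted, or that the data are insufficient.** This cannot be shown without the actual patients and events. The plan also includes split-sample and bootstrap checks and, as an alternative, hierarchical models with shrinkage.
- **That the claim fails drastically for 90-day death as a primary outcome.** Death within 90 days is named together with complication grade, and is not clearly a primary outcome on its own.

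**Conclusion.** The concern holds as a fault in the stated calculation. The 1180 figure carries no stated event fraction, is matched within one patient by a linear-regression test, and falls short for a single predictor at odds ratio 1.2 in logistic regression: 787 development patients against at least 945, with power of 72% at best and 53% at an assumed 20% event rate. These figures assume a per-standard-deviation odds ratio, no collinearity and a two-sided 5% test; collinearity or binary coding would raise the requirement.

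Thirty predictors is not shown to be the extreme case. The statement that the requirement lies well below the available sample is unsupported rather than disproved: the one count given suffices only at event rates of about 35% to 65%, and the larger CAMUS cohorts may prove adequate once counted.

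**What to change.** - Withdraw the 1180 and 80% power claim, or restate it with the test, the predictor scale and the event fraction named.
- State the patients and events held for each cohort and each modelled outcome.
- Recompute with a logistic or prediction-model criterion, using those event fractions and the full count of candidate parameters, including any indicator variables. Show a range for R². The range matters: for expected shrinkage of 0.90 with 30 parameters and 20% events, the development sample is about 2,693, 1,981 or 1,267 at an assumed Nagelkerke R² of 0.15, 0.20 or 0.30.
- Use the result to cap the candidates per model, or to require penalised estimation where the events do not support them.
- Make the statement in section 4.3 about stepwise selection conditional on that result.

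The cost is a recalculation on data already collected and some rewording. No further enrolment is needed. Some models may have to start from fewer candidate predictors.

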### Assessment of risk and difficulty factors

3.2

Risk factors affecting surgeon performance will be rated exclusively by surgeons, whereas those impacting the anaesthetist will be assessed solely by anaesthetists. Risk factors influencing both surgical and anaesthetic outcomes will be evaluated by both groups. Surgeons will assess parameters related to surgical difficulty and complication risk, while anaesthetists will focus on factors contributing to the risk of complications.

To enhance accessibility, the risk prediction index will primarily utilise routinely available preoperative patient characteristics and easily quantifiable intraoperative conditions. Each variable will be assigned a numerical value, with higher values indicating greater significance in determining outcomes.

As peri- and postoperative complications arise from both surgical and anaesthetic risk factors, input from both disciplines will be essential in developing the index.

To evaluate the association between proposed parameters and complications, and to estimate their likelihood, a nomogram will be constructed using data from the CAMUS Collaboration database, supplemented with parameters from a prospective open cystectomy database at the University of Bern. The likelihood of complications will be critical, as each parameter will be assigned a specific weight to be incorporated into the risk prediction score.

Institutional databases will be utilised to create a model predicting the impact of certain parameters on peri- and postoperative complications at 90 and 360 d after surgery. Additionally, organ-specific scoring systems for bladder, prostate, kidney, and testicular cancer will be developed using a nomogram and institutional databases.

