### Statistical analysis and development of the score

4.1

All statistical analyses will be conducted using R packages. Initially, a univariate analysis will be performed to examine the relationship between each pre- and intraoperative variable in the database and the primary outcomes. Variables with *p* ≤ 0.20 and ≤10% missing data will be considered for inclusion in a multivariable model, to ensure sensitivity and prevent the exclusion of potentially relevant factors. Among collinear variables, selection will be based on *p* values and their potential use in constructing an outcome score.

In the multivariable analysis, intraoperative variables will be entered independently and in combination with preoperative variables into a logistic regression model. Both forward and backward stepwise selection procedures will be employed (with entry criteria *p* ≤ 0.10 and inclusion criteria *p* ≤ 0.05) for outcomes of interest. The final model will be selected based on the Akaike Information Criterion (AIC). Variables that independently predict major complications or death will be considered as candidates for the risk index score. Alternative combinations of variables for the risk index score will be compared, emphasising simplicity, clinical safety, and predictive power.

After determining the final variables for inclusion, the magnitude of the β coefficients from the regression equation will be used to assign weights to each variable. Depending on the number of variables included, the score will be represented as either a 10-point or a 20-point scale. The intervals and cut-offs for each point level will be designed to ensure that a 1-point increase in the score corresponds to a proportional increase in the odds of a complication. The values for each cut-off will then be rounded to clinically relevant figures that can be recalled easily by surgeons. For instance, operation duration will be valued as follows: 0 points for ≤120 min, 1 point for 120–180 min, etc.

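### Excluding patients whose complication date is missing selects on the primary outcome, and the related 10% missing-data rules and imputation method are loosely or wrongly specified

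*Protocol article*

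**What the plan says.** All references are to the protocol article.

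- **Patient exclusions, section 3.7.** To limit selection bias, "the exclusion criteria were restricted to patients with ≤10% missing data and by age factor". Later in the same section, as a step already taken, patients are also excluded for missing critical variables, "such as the date of postoperative complication-intervention events, Clavien-Dindo complication (CDC) grade, or death within 90 d".
- **Primary outcomes, section 3.7.** "The primary study outcomes are the CDC/CAMUS grade or death within 90 d and the Comprehensive Complication Index (CCI").
- **Imputation, section 3.7.** "Missing data have been managed using imputation, specifically employing the" method of Buck.
- **Variable filter, section 4.1.** Variables with a univariate p value of at most 0.20 and "≤10% missing data will be considered for inclusion in a multivariable model".
- **Data sources.** The CAMUS cystectomy data hold "pre- and intraoperative variables sourced from 178 centres worldwide" (section 3.3). They are "supplemented with parameters from a prospective open cystectomy database at the University of Bern" (section 3.2), and a "comprehensive single-centre cystectomy database from the University Hospital Bern (*n* = 1550) is included" (section 3.7). The number of CAMUS patients is not given.

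**The concern.** A patient with no complication has no complication date to lose. Excluding on a missing date therefore removes patients only from the group with events. If a patient is dropped when any one date is missing, those with several events are the most likely to go, and they fill the upper end of the Comprehensive Complication Index, itself a primary outcome.

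Absolute risk is at stake. The calculator is meant for consent and for comparing surgeons and hospitals (section 5.1.2). If centres differ in how well they record dates, those that record poorly lose more of their complicated patients and look better. Neither the random two-thirds/one-third split (section 4.3) nor the comparison of two development years with the third year (section 4.1) would show this, because both use the same filtered data.

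Three further points concern the same missing-data scheme:

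- The patient-level 10% sentence, read literally, excludes the patients with the most complete records.
- The variable-level 10% filter could work against the stated purpose of adding the Bern parameters.
- Buck's method fills each gap with one regression prediction and treats it as observed, while p values from the completed data drive variable selection.

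**Working it through.** The plan states no figure for this point, so there is none to reproduce. Missingness rates and event rates below are assumptions.

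**1. Missing event date, taken alone.** Let r be the true event rate and m the share of patients with an event who are excluded.

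Observed rate = r(1 − m) / (1 − rm), so the odds are multiplied by (1 − m).

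| m (assumed) | r = 20% | r = 40% | r = 60% |
|---|---|---|---|
| 2% | 19.7% | 39.5% | 59.5% |
| 5% | 19.2% | 38.8% | 58.8% |
| 10% | 18.4% | 37.5% | 57.4% |
| 20% | 16.7% | 34.8% | 54.5% |

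Example: 0.20 × 0.90 / (1 − 0.02) = 0.18 / 0.98 = 18.4%.

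**2. Patients with several events.** Suppose each date is missing independently with probability 10%, and one missing date is enough for exclusion (both assumed). The chance of exclusion with k events is 1 − 0.9^k: 0% for none, 10% for one, 27% for three and 41% for five.

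**3. Odds ratios.** Let m1 and m0 be the exclusion shares among patients with events at two levels of a predictor. The odds ratio is multiplied by (1 − m1)/(1 − m0).

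- Equal shares: factor 1, no change.
- 10% against 5%: 1.20 × 0.90/0.95 = 1.14.
- 20% against 5%: 1.20 × 0.80/0.95 = 1.01.

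**4. The whole exclusion rule.** Suppose the other two parts also remove a share q of event-free patients. The observed rate is then r(1 − m) / [r(1 − m) + (1 − r)(1 − q)]. With r = 20% and m = 10%:

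- q = 5%: 0.18/(0.18 + 0.76) = 19.1%
- q = 10%: 0.18/(0.18 + 0.72) = 20.0%
- q = 15%: 0.18/(0.18 + 0.68) = 20.9%

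The net effect can go either way.

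**5. Bern-only parameters and the 10% filter.** In a pooled file with C CAMUS patients who lack the parameter, its missing share is C/(C + 1550). This is at most 10% only if C ≤ 1550/9 = 172.2, that is 172 patients. One patient from each of the 178 centres already gives 178/1728 = 10.3%; C = 1000 gives 39.2% and C = 5000 gives 76.3%. If the filter is applied within the Bern data, or after imputation, a Bern-only parameter does not fail for this reason.

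**6. Buck's method.** Simulations used n = 787 (two-thirds of the plan's 1180), 10% missing values and a true coefficient of 0.200.

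- Outcome in the imputation model, linear outcome: coefficient 0.222, standard error about 8% too small.
- Outcome in the imputation model, logistic outcome, five predictors: coefficient 0.214, standard error about 14% too small.
- Outcome left out, two predictors with correlation 0.5: coefficient 0.200 with a standard-error ratio of 0.96 (linear), and 0.204 with a ratio of 0.99 (logistic).

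The plan does not say whether the outcome was in the imputation model.

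**The case against.** **Direction and size.** A missing grade can mean that complication status was never recorded, and a missing 90-day death status can remove event-free patients lost to follow-up. A reader might infer that the whole rule makes the calculator under-predict. The documents do not support that: step 4 shows the net direction is open. Section 3.7 also describes trained, audited data collectors and standard definitions, so the share lost may be small. All of this stands. It does not alter the fact that the date part acts only on patients with events.

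**External validation.** The prospective cohort in section 4.4 could expose wrong absolute risks. That is fair, but it is a later phase, and it would help only if it did not apply the same exclusion.

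**The reversed inequality.** The sentence's own aim and the correct direction in section 4.1 make the intention evident. This stands: it is a wording error. The sentence also limits exclusions to missingness and age, which the separate critical-variable exclusion contradicts.

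**Bern parameters.** A reader might infer that no Bern-only parameter can ever enter the model. That requires one pooled file screened before imputation, and the article states neither. Section 4.1 speaks of two cystectomy cohorts, which leaves room for separate analysis, and parameters can also reach the indices through the Delphi weighting. The objection stands against the strong reading. What remains is that the denominator and order of the filter are not fixed.

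**Buck's method.** The coefficient bias appears only when the outcome is in the imputation model, so it is not a demonstrated error of this plan. What stands is that filled values are treated as observed.

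**Conclusion.** The concern holds in a limited form and should be fixed.

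- Exclusion on a missing complication date depends on the outcome. Alone, it multiplies the event odds by (1 − m); for a true rate of 20% and m from 2% to 20%, the observed rate falls to between 19.7% and 16.7%. Both the rate and m are assumptions, so the real size is unknown.
- Odds ratios are unaffected if date missingness is unrelated to the predictors. The net direction of the full critical-variable rule is not established.
- The patient-level 10% sentence is written the wrong way round, and its claim about which exclusions were used conflicts with the further exclusion in the same section.
- The variable filter would remove every Bern-only parameter if the files are pooled and screened before imputation, unless CAMUS contributes at most 172 patients. Neither condition is stated.
- Single deterministic imputation can understate the standard errors that feed the p-value selection. How much depends on details the article does not give.

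**What to change.** 1. Keep patients with a missing event date. Count the event where the grade is known and the existing records can establish that it fell within 90 days. Otherwise multiply impute the date window or the grade.
2. Report the analysis that excludes these patients as a sensitivity analysis, with the number excluded by outcome.
3. Reword the patient rule so that patients with more than 10% missing data are excluded, and list every exclusion in one place.
4. Apply the 10% variable filter within each database, state its order relative to imputation, and fit Bern-only parameters as a Bern extension model.
5. Replace Buck's method with multiple imputation that includes the outcome and centre.

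Cost: data preparation is rerun on existing data and the analysis text is revised. No new data are needed. The downside is that some outcome values are imputed and more computing is required.
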